*Secondary Outcomes:* To explore the characteristics of participants that predict improvement in sleep outcomes (Exploratory Aim 3), disability (assessed by the Patient-Determined Disability Steps; PDDS) [32], depression (assessed by the Patient Health Questionnaire; PHQ-9) [41], anxiety (assessed by the Generalized Anxiety Disorder Assessment; GAD-7) [49], sleep self-efficacy (assessed by the Sleep Self-Efficacy Scale; SESS) [50], and adherence to the intervention are also assessed. Disability level, depression, anxiety, and sleep self-efficacy have a known bidirectional relationship with sleep and fatigue and are plausible predictors of responders and non-responders to CBT-I.1.Patient-Determined Disability Steps (PDDS) [32] scale is used to assess disability. It consists of a 9-point scale ranging from “normal” (score of 0) to “bedridden” (score of 8). The PDDS has been validated and highly associated with the Expanded Disability Status Scale [33].2.Patient Health Questionnaire (PHQ-9) [41] is a valid and reliable method to assess depression during the past 2 weeks. It consists of 9 items with a score ranging from 0 to 27. A tenth question that is not included in the summary score assesses how depressive symptoms affect functional level. The PHQ-9 is used as a screening tool and an outcome measure.3.Generalized Anxiety Disorder Assessment (GAD-7) [49] is a valid and reliable method to assess anxiety over the past 2 weeks. This questionnaire consists of 7 items, and the score from each item is summed for an overall score ranging from 0 to 21 with a higher score indicating a higher level of anxiety. An additional eighth question assesses if anxiety impacts daily activities and sociability.4.Sleep Self-Efficacy Scale (SESS) [50] is a 9-item self-report questionnaire used to measure sleep self-efficacy. The respondents indicate confidence in ability to accomplish 9 sleep behaviors on a 5-point Likert scale with 1 = “not confident” at all to 5 = “very confident”. The score ranges from 0 to 45 with a higher score indicating greater sleep self-efficacy.5.Adherence to CBT-I intervention: To assess adherence to the CBT-I intervention, the sleep log is used to assess number of mornings per week the participant got out of bed at agreed upon time, number of times got out of bed if unable to sleep within 20 min, and number of nights per week the participant conducted wind-down routine. A total percentage will be calculated and used as the outcome of interest.

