#### Cognitive behavioral therapy for insomnia (CBT-I)

2.7.1

The CBT-I program is a 1x/week, 6-week one-on-one program via video conferencing (HIPAA-compliant Zoom). The program is based on standard CBT-I manuals [51,52]. Participants maintain a sleep diary during the program to aid in tailoring the program. Each session includes a summary and graphing of sleep diary data, an assessment of treatment gains and adherence, and determination if upward titration of total sleep time is warranted. The general session outlines are as follows with each session lasting 45–60 min:

*Session 1*: subjective sleep history and description of current sleep issues, education regarding physiological mechanisms of sleep using the two process of model of sleep [53] and 3P model of insomnia [54], and tailored sleep promotion techniques, collaboratively set time in bed restriction, discuss strategies for stimulus control (if fall risk, perform counter-control in bed instead), discuss avoiding/limiting naps (limit napping to ≤ 30 min, to take the nap as early in the day as possible, and delaying bedtime to a later time may be necessary until they were adequately tired).

*Session 2*: review sleep promotion techniques, introduce diaphragmatic breathing and deep breathing as relaxation techniques to reduce pre-sleep arousal.

*Session 3*: introduce mindfulness as a technique to reduce pre-sleep arousal.

*Session 4*: introduce progressive muscle relaxation (PMR) as relaxation technique to reduce pre-sleep arousal (if concern about contraction portion of PMR may increase symptoms or spasticity, recommend only performing relaxation strategies).

*Session 5*: cognitive restructuring for negative sleep beliefs as needed, reinforce and/or continue to tailor various techniques.

*Session 6*: discuss relapse prevention and maintenance of sleep gains.

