#### Active control group (control)

2.7.2

The control group matches the intervention group for time, contact with research personnel, and delivery method. The control group receives basic sleep hygiene and lifestyle education which is very commonly used as the control for CBT-I. Importantly, participants in the control condition do not receive active components of CBT-I (i.e. time in bed restriction, stimulus control, cognitive restructuring, relaxation strategies, psychoeducation) or strategies to change sleep behavior (i.e. motivational interviewing, goal setting for sleep). The control program is a 1x/week, 6-week one-on-one program via video conferencing (HIPAA-compliant Zoom). The general session outlines are as follows with each session lasting 45–60 min and includes starting the session with basic stretches and ending the session with same stretches:

Session 1: education on sleep stages.

Session 2: education on sleep hygiene (focus on environment of temperature, noise, light, optimal sleeping positions).

Session 3: education on sleep hygiene (focus on stimulants/depressants of caffeine, medications, nicotine, alcohol, screen time).

Session 4: education on sleep hygiene (focus on diet/nutrition of large/spicy meals, fluid intake, basic diet recommendations).

Session 5: education on sleep hygiene (focus on exercise).

Session 6: discuss remaining questions.

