#### Exploratory Aim 3: To explore the baseline characteristics of participants that predict improvement in sleep outcomes

3.2.3

HypothesisBaseline disability level, anxiety, depression, and sleep self-efficacy will predict responders and non-responders (i.e. higher disability, anxiety, and depression, lower sleep self-efficacy, and lower intervention adherence will predict non-responders; lower disability, anxiety, and depression, and higher sleep self-efficacy and level of intervention adherence will predict responders).

*Statistical Plan*: For Aim 3, the outcome is dichotomous (responders vs non-responders) and a logistic regression analysis will be conducted modeling responder status (defined as meeting the minimal clinically important difference of ≥ 6 points on the ISI) at 6 weeks. This will allow assessment of the effect of baseline predictors such as disability level, anxiety, depression, sleep self-efficacy level, and intervention adherence. The analysis will be conducted at the 5 % level of significance.

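### Aim 3 lists intervention adherence as a baseline predictor, but it is scored during treatment, and apparently only for CBT-I

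*Protocol article*

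**What the plan says.** Section 3.2.3 gives the aim as "To explore the baseline characteristics of participants that predict improvement in sleep outcomes". Under its statistical plan, "a logistic regression analysis will be conducted modeling responder status" at 6 weeks, with response defined as at least 6 points on the ISI. It continues: "This will allow assessment of the effect of baseline predictors such as disability level, anxiety, depression, sleep self-efficacy level, and intervention adherence". It closes with "The analysis will be conducted at the 5 % level of significance". It does not say whether one arm or both are analysed, and treatment arm is not among the predictors named.

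The hypothesis in the same section opens by attaching the word baseline to four variables only: disability, anxiety, depression and sleep self-efficacy. Adherence is added in the parenthesis that follows.

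Section 2.5, item 5, defines the measure: "To assess adherence to the CBT-I intervention, the sleep log is used to assess number of mornings per week" that the participant rose at the agreed time, together with getting out of bed when unable to sleep and evenings with a wind-down routine. "A total percentage will be calculated and used as the outcome of interest". Table 2 labels it as adherence to the CBT-I protocol.

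Section 2.7.1, on the CBT-I arm, states: "Participants maintain a sleep diary during the program to aid in tailoring the program". Section 2.7.2 states that "participants in the control condition do not receive active components of CBT-I", and mentions no diary or log for controls.

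**The concern.** A baseline predictor must be known before treatment starts. The Introduction and Discussion want Aim 3 to help patients and clinicians choose a sleep intervention for the individual. Adherence is unknown when that choice is made, so an odds ratio for it cannot serve that purpose.

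Two further consequences follow from how the measure is built.

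- **Timing.** Adherence accrues over the same six weeks in which the response develops. Its association with response may run partly from response to adherence.
- **Arm.** If the score exists only for CBT-I, a model that includes it either has no usable control records or needs an invented value for them. A placeholder such as 0, with no arm term, would let adherence carry the difference between arms.

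At stake is what Aim 3 can report: adherence could be presented as a patient characteristic that predicts response, and the four real baseline predictors could be estimated on very few non-responders.

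**Working it through.** **Inputs.** Section 3.1: 35 per arm; ISI mean change 13.8 (CBT-I) and 8.1 (control), common SD 5.8; correlation 0.5 between the two follow-ups; two-sided 5%; 90% power; 25% attrition. Section 3.2.3: response threshold 6 points. Assumed: normal change scores, and planning means that apply at 6 weeks.

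**The plan's own figure.** Aim 3 has no sample size of its own, so the check is whether the ISI inputs reproduce the plan's 17 per arm:

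n = 2 × (1.960 + 1.282)² × 5.8² × (1 + 0.5)/2 ÷ (13.8 − 8.1)² = 16.3, rounded up to 17. This matches.

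**Responder rates.** P(change ≥ 6) = 1 − Φ((6 − mean)/5.8).

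- CBT-I: 1 − Φ(−1.345) = 91.1%.
- Control: 1 − Φ(−0.362) = 64.1%.

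**Expected non-responders.**

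- CBT-I arm: 35 × 0.0893 = 3.1. With five predictors, 3.1/5 = 0.6 per predictor.
- Control arm: 35 × 0.3587 = 12.6.
- Both arms: 3.1 + 12.6 = 15.7 of 70, or 15.7/5 = 3.1 per predictor.

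**CBT-I-only model.** CBT-I arms of 35 were simulated with five independent normal predictors, counting data sets with separation or no non-responder at all. Repeated runs gave 26 to 28%. The result depends strongly on the true mean change:

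| True CBT-I mean change | Non-responders of 35 | Separation or none, five predictors |
|---|---|---|
| 13.8 | 3.1 | about 27% |
| 12 | 35 × Φ(−1.034) = 5.3 | about 5 to 8% |
| 10 | 35 × Φ(−0.690) = 8.6 | about 1% |

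At 13.8, dropping adherence but staying in the CBT-I arm still leaves about 18 to 19% with four predictors. The sparsity therefore comes mainly from the restriction to one arm.

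**Two-arm model with controls coded 0 (illustrative; not in the plan).** Adherence in CBT-I was drawn with mean 0.85 and SD 0.12 (assumed), with no effect on response within the arm. With 35 per arm and no arm term, adherence is significant at 5% in about 73% of simulated trials. Across assumed adherence means of 70 to 93% the range is 64 to 74%. With arm added, it falls to about 2% or less.

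**Attrition.** Section 3.1 ties the 25% to the delayed reassessment, while Aim 3 uses the 6-week outcome. So 35 × 0.75 ≈ 26 per arm is a pessimistic bound. At that bound there are 26 × 0.0893 = 2.3 non-responders in CBT-I, and separation or none occurs in about 46 to 48% of data sets.

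**The case against.** The strongest reply is that a CBT-I-only analysis is what the authors intend. Section 2.5 describes these variables as likely predictors of who responds to CBT-I, and adherence is defined for CBT-I. Leaving out the controls would then be a design choice. This stands as a plausible reading. It does not rescue the baseline label, section 3.2.3 does not state it, and it leads to the model with about three non-responders.

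Several stronger readings are tempting and should not be drawn.

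- *That the plan will code controls as 0.* Nothing says so. The predictor list is introduced as examples, so an arm term is possible and would largely remove the proxy problem. Adherence would still be measured after randomisation and lack a defined value in controls.
- *That adherence is a consequence of response.* The documents do not show this. One item counts getting out of bed when sleep does not come, and better sleepers have fewer such occasions, so the direction of any bias in the total percentage is unclear.
- *That the model will usually fail to fit.* The 27% rests on a 13.8-point mean change from pilot arms of 10, and the risk shrinks quickly at smaller changes.

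Aim 3 is also exploratory, and the opening of its hypothesis reserves baseline for the right four variables, so loose wording may explain part of this. That limits the severity. The plan sentence still enters adherence in the same model, tested at 5%.

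**Conclusion.** The point holds as an internal contradiction with analytic consequences. A measure taken after randomisation, concurrent with the outcome and defined for CBT-I, is listed as a baseline predictor in an aim about baseline characteristics. That it has no value in controls is inferred from sections 2.5, 2.7.1 and 2.7.2.

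Its size depends on the unstated analysis population. A CBT-I-only model has about 3 non-responders of 35, where both arms together would give about 16 of 70. Separation or no non-responder occurs in about 27% of five-predictor fits at the planning mean, and in about 1 to 8% if the true mean change is 10 to 12. The 73% rate of spurious significance applies only to controls coded 0 with no arm term. These figures assume normal change scores, SD 5.8 and independent predictors.

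A reader might infer that every version of the Aim 3 model is invalid. The documents do not support that: a CBT-I-only analysis that treats adherence openly as a post-randomisation measure would be legitimate, though sparse. Aims 1 and 2, the primary ISI analysis and the sample size are untouched. The change is worth making, but it is not critical to the trial.

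**What to change.** In section 3.2.3, and in the full analysis plan:

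1. Remove intervention adherence from the list of baseline predictors and from the Aim 3 hypothesis.
2. State the analysis population. Fit the four baseline predictors (PDDS, GAD-7, PHQ-9, SESS) on both arms with treatment arm in the model. The arm term is needed because the planning values imply responder rates of 91% and 64%.
3. If predictors of response to CBT-I specifically are meant, add arm-by-predictor terms and label them exploratory.
4. Report adherence separately within the CBT-I arm, as a descriptive post-randomisation association with response.

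The cost is a change of wording and no new data. The loss is that adherence is described and no longer tested as a predictor. The revised model is still thin: four predictors plus arm give 15.7/5 = 3.1 non-responders per term, and adding four interactions gives 15.7/9 = 1.7, so estimates should be read with their confidence intervals.

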## Discussion

4

Insomnia is a common problem in people with MS [4], which often remains unrecognized and therefore untreated [5]. CBT-I has been shown to be highly effective in addressing sleep disturbances in people with primary insomnia [19,20], as well as in populations of people with insomnia comorbid with a variety of chronic conditions [18]. However, evidence on the efficacy of CBT-I for pwMS remains limited. Our previous pilot studies demonstrated feasibility and large improvements in sleep outcomes in pwMS following CBT-I [28,29]. The proposed study represents the next needed step to determine the efficacy of CBT-I in this population. Specifically, we will conduct an adequately powered prospective randomized control trial (RCT) to assess the efficacy of CBT-I delivered via telehealth compared to an appropriate control group to improve sleep outcomes (Aim 1) and fatigue and health-related quality of life (Aim 2). An Exploratory Aim 3 will determine the participant characteristics that predict improvement in sleep outcomes. This will help guide health care providers and individuals with MS to select an appropriate sleep intervention at an individual level. Addressing insomnia symptoms using CBT-I could represent a low-cost, low-risk, non-pharmacological option for improving sleep quality, fatigue, and quality of life in individuals with MS and could result in reduced disability, improved quality of life, increased employment, and reduced costs associated with care and support for individuals with MS.

### Anticipated challenges and limitations

4.1

Recruitment of individuals with a disability for clinical trials is often challenging. The proposed study will be conducted completely remotely across the United States which will increase the likelihood of successful recruitment. This will also enhance generalizability of the results. Another potential difficulty relates to the fact that individuals will enroll in this study for a period of 6 months which can pose a challenge to adherence to the principles learned from the intervention as well as retention in the study. In our recent pilot study of one-on-one in-person CBT-I in individuals with MS [28], retention was excellent; the CBT-I group had a retention rate of 83.3 % and adherence rate was or 93.3 %. Due to high comorbidity rates between depression and insomnia, excluding participants with severe depression can also be viewed as a limitation as this will likely restrict the variability in the range of scores for the Aim 3 analysis. Further, because individuals with untreated sleep disorders or elevated sleep apnea risk were excluded, findings may not generalize to people with MS who have co-morbid insomnia and sleep apnea. Although CBT-I can be effective in co-morbid insomnia and sleep apnea when obstructive sleep apnea is concurrently managed [55], this trial was not designed to assess or treat sleep apnea. Finally, exclusion of individuals with a history of overnight shift work within the last 5 years may be conservative, as long-term sleep disruption following shift work is not well established and it may therefore limit generalizability of the results.

## Conclusion

5

While insomnia is a highly prevalent in individuals with MS, there is a critical need for an effective non-pharmacological intervention option to become more widely available. The current project will address this critical knowledge gap by addressing insomnia symptoms through CBT-I which will offer a low-cost, low-risk, non-pharmacological option for improving sleep quality and fatigue in individuals with MS.

## Data Availability

No data was used for the research described in the article.
